### Study design

SMILe-ICM will be tested using a hybrid effectiveness-implementation randomised controlled trial (RCT) [68]. While the evaluation of the novel SMILe-ICM’s effectiveness regarding primary and secondary outcomes will be our central concern, the chosen design will also allow us to evaluate the bundle of implementation strategies by assessing implementation outcomes and the implementation pathway. This approach will allow us not only to plan further SMILe-ICM scale-ups to other settings, but also to inform the fine-tuning of the intervention and our bundle of implementation strategies. Figure 3 highlights the SMILe hybrid design, including its enrolment, allocation, randomization (see also below) and measurement time-points. The SMILe study was registered via ClinicalTrials.gov: NCT04789863 and approved by the responsible ethics committee (Ethics Committee Northwest and Central Switzerland (EKNZ: 2021–00202)). We describe the methods of the evaluation of the SMILe-ICM based on the SPIRIT guidelines [69].

**Fig. 3 Fig3:**
[figure not shown]
The Hybrid effectiveness-implementation RCT study design. Note. QUAL = qualitative methods; QUAN = quantitative methods; RCT = randomised controlled trial; *Timepoints data collection T0b–Tz (±7 days)

### Context and targeted sites

In Switzerland, nearly 250 alloSCTs are performed annually. Roughly 110 of these take place at the USB, which is the largest alloSCT program in Switzerland [70]. The USB has a designated alloSCT unit and outpatient clinic, as well as a specialised alloSCT medical and nursing staff. Patients are hospitalised about 10 days before their transplantation. After it, depending on their state of health, they remain in hospital an average of 25 days. As noted, post-transplant monitoring and care follow an outpatient follow-up schedule. Depending on the patient’s state of health, post-transplant care then can be transferred to closely-collaborating external centres. Patients from the Switzerland’s Italian-speaking region (Ticino) receive their follow-up care solely at the haematology departments closest to their homes.

One issue revealed by the current study’s contextual analysis (Phase A) is that, once patients are discharged, they receive a low mean level of chronic illness management including limited self-management support. The clinician group most qualified to remedy this shortfall would be the APNs. However, while they are involved in immediate post-transplant care and discharge planning, longer-term post-transplant management is not yet organised as a multidisciplinary topic.

An academic service partnership between the USB and the University of Basel’s Institute of Nursing Science (INS) provides the infrastructure that supports the SMILe project. Two of the SMILe investigators (SV, JR) work in joint INS/USB appointments.

According to the Swiss Federal Law on Health Insurance, health insurance covers all allowable costs of medical treatment and hospitalisation. The patient’s deductible amounts and co-payments can only be used towards these costs [71]. This system creates a problem for eHealth innovations. While eHealth is promoted at the policy level in Switzerland, major heterogeneity in operational systems hinders easy roll-out of eHealth interventions [72, 73]. And, although digitization financing is promoted within the “Swiss eHealth Strategy 2.0 2018-2022” [29], no nationwide compensation models currently enable billing and remuneration for telemedicine [73]. This means that no provision currently exists to compensate either eHealth nor APNs for their work monitoring alloSCT recipients’ daily reports. Health-Apps can currently neither be prescribed nor paid for by health insurances [74], as it is already the case in other countries [75].

### Study participants, recruitment, and randomization

#### Sample

To reach Aims 1 and 2, both patients and members of the alloSCT team will be recruited respectively as this study’s subjects and as its data collectors. For aim 1, all adult alloSCT patients scheduled for transplantation at the USB Department of Haematology will be invited to participate in this study. They will be eligible if (1) they have basic German language proficiency and basic computer literacy; (2) they are to be both transplanted and followed-up at USB; (3) they have internet access at home; (4) they are able to carry out self-management tasks. Patients will be excluded if (1) they have cognitive dysfunction, hearing impairment or any handicap precluding use of the necessary technology and/or active participation in face-to-face visits; (2) they are scheduled to receive their second alloSCT within 1 year.

A purposive sample of alloSCT team members (i.e., haematologists, nurses, psycho-oncologists, managers) involved in in-patient and follow-up care will be invited to participate in surveys and focus group interviews. These will be used to evaluate the bundle of implementation strategies by respectively the implementation outcomes and the evaluation of the implementation pathway (Aim 2).

#### Sample size determination for aim 1

In order to determine an appropriate patient sample size, we considered the USB’s baseline hospitalisation event rate per patient year. As exact patient year data are not available, we assumed that in any given year, each transplant patient year receives roughly 0.5 patient years of care. We based our calculations on Schenkel et al.’s [6] study, which used patient years (number of hospitalisation events per patient year (HEPPY)) as an outcome for an intervention in lung transplantation.

The hospitalisation rate consists of two elements: the number of hospitalisations and the period (in years) over which patients are followed up. We conducted simulations using the paramtest software package [76], computing 10′000 iterations of the chosen parameters. Based on the USB’s available data, we set the hospitalization events per patient year to 1.56. The study’s observation period is 15 months (1.25 years). We determined the minimum sample size using the inverse of the effect size in Schenkel et al. [6], i.e., 1.79 [1.31–2.43]. Following Olivier et al.’s guidance [77], we aimed for the upper bound of a small effect size. The simulation is based on a binomial distribution with a shape parameter of 4. Assuming an α level of 0.05, a power of 80% and an effect size of 1.79, a minimum sample size of 52 patients (26 per group) was determined. Based on a refusal rate of 10% and a 15% drop out rate, then, we will aim to recruit a total of 80 patients (40 per group). Considering that approximately 70 adults per year receive *both alloSCT and follow-up* at USB, recruitment will take a minimum of 16 months.

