**Aim 1** has two parts**:**

**1a.** to evaluate the SMILe-ICM’s effectiveness in view of one primary outcome—re-hospitalisation rate—and seven secondary outcomes—total healthcare utilization costs, total length of inpatient re-hospitalizations, medication non-adherence, treatment burden, health-related quality of life (HRQL), quality-adjusted life year (QALY), acute and chronic GvHD incidence and grade, and overall survival rate. Regarding the primary outcome, we hypothesise that, compared to the usual-care/control group, patients receiving the SMILe-ICM will have a lower re-hospitalisation rate. As for the secondary outcome set, compared to the control group, we expect to see lower total healthcare utilization costs, shorter lengths of re-hospitalizations, lower medication non-adherence (implementation phase of adherence [67]), less treatment burden, better HRQL, higher quality-adjusted life years (QALY), and equal medical outcomes (acute and chronic GvHD incidence, overall survival).
**1b.** to extend objective **1a** by testing for a potential wane-out of the SMILe-ICM intervention effect in view of primary and secondary outcomes during the three-month post-intervention follow-up.
**Aim 2** is to evaluate the SMILe–ICM’s bundle of implementation strategies and assess acceptability, appropriateness, feasibility, and fidelity (implementation outcomes) as well to evaluate the implementation pathway (as viewed by patients and health care professionals).

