#### Analysis

Statistical analyses will be conducted at the University of Basel’s Institute of Nursing Science using the R software package [96]. Data cleaning will include systematic screening for out-of-range values and data inconsistencies. Multiple imputations will be considered for missing data. Descriptive statistics will be applied as appropriate for all variables.
***Aim 1a:*** To determine whether hospitalisation rates (primary outcome) are reduced via the SMILe-ICM’s implementation, we will analyse any differences between IG and UCG rates by applying generalised linear mixed models (GLMM) [97]. The relevant variables (i.e., time, study group, and group x time interaction) will be entered into the models. Our targeted test statistic is the rate ratio by unconditional maximum likelihood estimation (Wald) as described by Rothman et al. [98] and implemented in epitools [99]. We will conduct intention-to-treat and per-protocol analysis. Two-sided significance will be set at 0.05. To analyze the target secondary outcomes over the course of time, descriptive analyses will be carried out and GLMM will be used to determine differences between the IG and UCG. Cost data will be collected and analysed quarterly. Overall survival will be analysed using the Kaplan-Meier method and the log-rank test. To analyse QALY, we will use the EQ-5D-5L**©** value set for Germany. The electronically compiled dosing history will be analysed using by applying GLMM, which account for dependence among observations from a single patient over time. The resulting estimates will be expressed as odds ratios (ORs) [100].
***Aim 1b:*** To test a potential wane-out effect of the SMILe-ICM’s intervention effect over 3 months’ post-intervention follow-up, differences between the IG and the UCG will be determined by applying GLMM. This approach allows calculation of the main group and time effects, and of group-by-time interaction effects. Two-sided significance will be set at 0.05.

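### The stated 80% power with 52 patients does not hold for the reduction in re-hospitalisations that the trial hypothesises

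*Protocol article*

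**What the plan says.** Under Sample size determination for aim 1, the protocol article starts from the site's "baseline hospitalisation event rate per patient year" and says "we set the hospitalization events per patient year to 1.56". It gives an observation period of 15 months (1.25 years). On the effect it says "We determined the minimum sample size using the inverse of the effect size" of a cited lung-transplant study, which is 1.79. On the model it says "The simulation is based on a binomial distribution with a shape parameter of 4". The result is "a power of 80% and an effect size of 1.79, a minimum sample size of 52 patients (26 per group) was determined". Allowing for 10% refusal and 15% dropout, it plans to recruit 80 patients, 40 per group.

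Three other places bear on this:
- Aim 1a hypothesises that "patients receiving the SMILe-ICM will have a lower re-hospitalisation rate".
- The Analysis section names a Wald rate ratio as the target statistic and states "Two-sided significance will be set at 0.05".
- Table 3 defines the primary outcome as re-hospitalisations after the initial discharge within the first year after transplant, not over 15 months.

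**The concern.** A ratio of 1.79 and its inverse have the same absolute logarithm, but they do not need the same sample size. The precision of a log rate ratio depends on the number of events. Starting from 1.56, a fall to 0.87 yields far fewer events than a rise to 2.79. If the inverted ratio is applied to the usual-care rate without reversing the direction, power is overstated.

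This is the only power statement for the only primary outcome. If it is too high, a null result may be read as stronger evidence of no effect than the design can give.

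**Working it through.** **Inputs.** Usual-care rate 1.56 per patient-year, ratio 1.79, 15 months, shape 4 and 26 per group (sample size section); reduction (Aim 1a); Wald rate ratio, two-sided 0.05 (Analysis); 1:1 allocation. A binomial has no shape parameter, so 4 is read as the negative binomial size k; this is an assumption. One year is also used because Table 3 limits the outcome to the first year. With the average post-transplant stay of 25 days given in the article, time at risk is about (365 − 25)/365 = 0.93 year, so the one-year figures are slightly generous.

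**Formulas.** Let m0 and m1 be the expected events per patient in each group, n the number per group, and ln 1.79 = 0.582.
- Variance used by the Wald test: P/n, with P = 1/m0 + 1/m1.
- Variance under a negative binomial with k = 4: T/n, with T = P + 2/4.
- Wald test power ≈ Φ[(0.582 − 1.96√(P/n)) / √(T/n)].
- Power of a test using the correct variance ≈ Φ[0.582/√(T/n) − 1.96].
- n per group for 80% with the correct variance: (1.96 + 0.84)² × T / 0.582².

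The Wald figures below come from simulation (100,000 runs or more per setting); the formula agrees within about one percentage point.

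**Reproducing 26 per group.** Take a rise from 1.56 to 1.56 × 1.79 = 2.79 over one patient-year.
- P = 0.641 + 0.358 = 0.999 and T = 1.499. At n = 26 the formula gives Φ[(0.582 − 0.384)/0.240] = 79.5%.
- Simulation gives about 79% at 25 and 80.3% at 26, so the minimum is 26.
- Over the stated 1.25 years, the same rise needs only 22 per group.

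**The hypothesised reduction, 1.56/1.79 = 0.87, at 26 per group.**
- 15 months: m0 = 1.95, m1 = 1.09, expected events 50.7 and 28.3; P = 1.431, T = 1.931. Wald: Φ[(0.582 − 0.460)/0.273] = 67%; simulation 68%. Correct variance: Φ[0.582/0.273 − 1.96] = 57%.
- One year: m0 = 1.56, m1 = 0.87, expected events 40.6 and 22.7; P = 1.788, T = 2.288. Wald: 59%; simulation 60%. Correct variance: 50%.
- Other distributions with the same two-sided Wald test: Poisson 71% (15 months) and 61% (one year); literal binomial of size 4, 76% and about 63%.

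**Type I error.** The Wald variance omits the 2/k term. With equal rates and k = 4, the simulated type I error is about 9% (one year) and 11% (15 months) against a nominal 5%, so the Wald powers are flattering.

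**Number per group for 80% power for the reduction.** Wald: 36 (15 months) or 44 (one year). Correct variance: 7.85 × 1.931/0.339 = 44.7, or 7.85 × 2.288/0.339 = 53.0.

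**Power with the 80 patients planned.** The second pair of rows takes 15% dropout with no data contributed, 40 × 0.85 = 34.

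| n per group | Test | 15 months | One year |
|---|---|---|---|
| 40 | Wald | 84% | 77% |
| 40 | Correct variance | 75% | 68% |
| 34 | Wald | 79% | 70% |
| 34 | Correct variance | 69% | 61% |

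**From 52 to 80.** The stated losses give 52/(0.90 × 0.85) = 68, not 80. Refusals also occur before randomisation and do not reduce the number analysed.

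**The case against.** Four points deserve weight.

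**Cause.** A reader might infer that the sponsor simulated a rise. The article never says so and the code is not shown. The match at 26 also needs one patient-year in place of the stated 1.25 years, so two inputs must change, not one. The mismatch stands; its cause remains an inference.

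**Other readings.** It would be too strong to say that no reading reaches 80%. The sample size section gives alpha as 0.05 without a side. For the reduction at 26 per group over 15 months, a one-sided 5% Wald test gives 77% (negative binomial), 81% (Poisson) or 87% (binomial of size 4), and a one-sided Poisson formula needs 26.1 per group. These conflict with the two-sided level in the Analysis section. A literal binomial of size 4 with its own variance needs 21.6 per group over 15 months on the log-ratio scale, or 27.0 over one year as a difference in means. Neither uses the variance of the planned Wald rate ratio, and both cap each patient at four events.

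**The trial recruits 80, not 52.** A reader might infer that the trial as run would miss a true 44% reduction (1 − 1/1.79) far more often than 20% of the time. That holds for 52 patients. With 40 per group, 15 months and the Wald test, power is 84%. Dropouts also contribute person-time: if 15% leave at uniformly spread times (an assumption), Wald power is about 82% over 15 months and 74% over one year. Against this, the Wald test exceeds its nominal level under the assumed model, and the primary outcome covers the first year only.

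**The step to 80.** Recruiting more than the stated losses require helps power. This is a matter of explanation, not a harm.

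**Conclusion.** The statement that 52 patients give 80% power is wrong for the stated hypothesis and the stated two-sided Wald rate ratio. At 26 per group, power is about 68% over 15 months and 60% over one year, or 57% and 50% once the assumed overdispersion enters the test. Poisson or literal binomial counts with the same Wald test give 61% to 76%.

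For the 80 patients planned, the shortfall runs from none (84%: Wald, 15 months, no dropout) to about 19 points (61%: correct variance, one year, 34 per group). The documents do not support a single achieved figure, because they do not jointly fix the window, the test's variance and the handling of dropouts. The negative binomial figures rest on reading the shape parameter as k = 4.

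**What to change.** Keep 80 patients. In the sample size section:
1. Re-run the simulation with 1.56 versus 0.87 events per patient-year, and state both rates so that the direction is explicit.
2. Use the at-risk window of the primary outcome in Table 3, from discharge to one year after transplant, and state how deaths and dropouts contribute person-time.
3. Name the distribution as negative binomial with its dispersion value, and use a test that allows for that overdispersion.
4. Replace the claim of 80% power with 52 patients by the power at the planned number, or by the ratio detectable with 80% power, shown by window and test where these are still open.
5. As a minor point, say how 80 was chosen, since the stated losses give 68.

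The cost is a re-run of existing code and a change of wording. No extra patients are needed. The downside is that the stated power becomes less favourable.

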#### Recruitment

The project leader of the SMILe project at USB (SV, shared first author), will screen potentially eligible participants. Eligibility criteria (see above) were kept as broad as possible to more closely approximate “real” patients. Following review of prospective participants’ medical records, those who meet the study’s inclusion criteria will be invited to participate. Written informed consent forms will be obtained from all participants before enrolment. These will be stored safely in the Investigator Site File. Patients have the right to withdraw from the study at any time without consequences.

#### Randomization process

Intervention patients will receive standard care plus the SMILe-ICM. The usual care group (UCG) will receive standard care. Patients will be randomly allocated 1:1 to the intervention group (IG) or UCG at hospitalisation, i.e., approximately 10 days pre-transplant. Randomization will be stratified by risk group according to age (>/< 65 years), gender (male/female) and living alone (yes/no). The concealed randomization procedure will be implemented via the secuTrial® web-based clinical data management system provided by the USB’s Clinical Trial Unit. After randomization and allocation, no further blinding will be feasible in any group. The study’s duration will be from approximately 10 days pre-transplant to one-year post-transplant, with 3 months’ follow-up after cessation of the intervention period to test for a wane-out effect. A CONSORT flowchart for patients is presented in Fig. 4.

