#### Intervention group (IG)

The intervention, i.e., the SMILe-ICM as described above and shown in Fig. 2, will be delivered by eHealth and care coordinators (CCs). The four CCs will be specially-trained APNs. In addition to holding Master’s degrees in nursing, all CCs will be experienced alloSCT experts. Prior to study start, a six-day training segment has been provided by the USB’s SMILe project leader (SV, shared first author) in March 2021. The IG participants will receive care as usual *PLUS* the SMILe-ICM (as described above).

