#### Data collection and management

Data will be collected at pre-defined time points from April 2021 until March 2024 (T0-Tz, see Table 2) by trained APNs using a standardised method in the IG and by one research assistant (using the same method) in the UCG. SMILe data will be de-identified with access limited only to authorized research study team members.

**Table 2 Tab2:** Variables, measurement and data collection points

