**Primary outcome**												
Re-hospitalisation rate (number of re-hospitalisations per patient year)	FIMA**©** (10 Items) [83] Medical Records, CRF											

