**Primary Outcome**		
Re-hospitalisation rate	Number of events after the initial post-alloSCT discharge per patient in the first year post-alloSCT	EHR

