The current study includes some risk of contamination bias: while the SMILe–ICM will be tested in an RCT, after the patients are randomised into UCG and IG, they will receive their care from the same alloSCT team. To minimise this risk, the APNs/CCs will only have contact with the IG participants. While this approach will not fully exclude the possibility of contamination, it will reduce it to an acceptable level. Admittedly, a cluster randomised approach would reduce this risk further; yet, given the importance at this stage of the SMILe–ICM’s development of establishing its effectiveness, the RCT design will be adequate.

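### The statement that no blinding is feasible after allocation is reasonable for patients and care staff, but it need not cover classification of re-hospitalisations or the primary analysis

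*Protocol article*

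**What the plan says.** All references are to the protocol article.

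- **Blinding.** Randomization process describes concealed 1:1 allocation through secuTrial, provided by the hospital's Clinical Trial Unit, and then states: "After randomization and allocation, no further blinding will be feasible in any group". No exception is made for outcome extraction or analysis.
- **Primary outcome.** Table 3 defines it as "Number of events after the initial post-alloSCT discharge per patient in the first year post-alloSCT", with the EHR as the only source. Table 2 lists the FIMA self-report questionnaire together with "Medical Records, CRF".
- **Who collects data.** Data collection and management says this is done "by trained APNs using a standardised method in the IG and by one research assistant (using the same method) in the UCG". Intervention group (IG) says of the care coordinators (CCs): "The four CCs will be specially-trained APNs". The Discussion adds that "the APNs/CCs will only have contact with the IG participants".
- **Who analyses.** The Analysis section places the statistical work at the university's Institute of Nursing Science. Context and targeted sites describes that institute as a partner in the project. Analysis names both a mixed model and a Wald rate ratio for the primary outcome, plans intention-to-treat and per-protocol analyses, and says: "Multiple imputations will be considered for missing data".

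**The concern.** The sentence is a statement about what is feasible, and nothing in the article supports it for two steps. A list of admissions and discharges can be drawn from the EHR without the arm. An analyst can work with a coded arm variable while secuTrial holds the key.

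Two features of the plan make those steps worth masking.

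1. **Ascertainment differs by arm.** The IG collectors belong to the profession that delivers the intervention, and usual care has a different collector. Neither is described as masked. If one collector captures or classifies stays more completely than the other, the difference goes straight into the rate ratio.
2. **There is some room to classify.** The primary definition counts events without saying whether planned stays are included, while Table 3's length-of-stay outcome explicitly includes planned and unplanned days. Tables 2 and 3 also differ on the sources for the primary outcome.

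The stake is a modest inflation of the chance of a false positive result, and weaker credibility for a single-centre, open-label result analysed within the project partnership.

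**Working it through.** The article gives no figure for the effect of unmasked counting, so there is none to reproduce. The check asks how much a small difference in counting between the arms would matter.

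**Inputs**
- 40 patients per arm; 1.56 hospitalisations per patient-year; rate ratio 1.79; shape parameter 4 (Sample size determination for aim 1). The article calls the distribution binomial; it is read here as negative binomial with dispersion 1/4 = 0.25, which is an assumption.
- One year of follow-up (Table 3). Wald rate ratio, two-sided 0.05 (Analysis).
- Share of IG stays missed: 0%, 5% or 10%. This is an assumption; the article gives no figure.

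**Step 1. Differential under-count with no true effect.** Expected stays per arm: 40 × 1.56 = 62.4, so 5% is about 3 stays and 10% about 6. Simulated negative binomial counts, tested with z = ln(a/b)/√(1/a + 1/b), where a is usual care and b is IG, gave:

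| IG stays missed | Significant result favouring IG |
|---|---|
| 0% | 4.8% |
| 5% | 7.5% |
| 10% | 11.4% |

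A normal approximation agrees. For 5% missed, the shift is −ln(0.95) = 0.0513. The Wald standard error is √(1/62.4 + 1/59.28) = 0.1814. The true standard error adds 2 × 0.25/40 = 0.0125 to the variance and is 0.2131. P(Z > (1.96 × 0.1814 − 0.0513)/0.2131) = P(Z > 1.43) = 7.7%. The same steps give 4.8% for none missed and 11.8% for 10%.

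The starting 4.8% exceeds the nominal 2.5% in one direction because the Wald formula ignores the assumed overdispersion. That is not a blinding effect. With Poisson counts the approximation gives 2.5%, 4.7% and 8.3%: for 5% missed, P(Z > 1.96 − 0.0513/0.1814) = P(Z > 1.68). The increase is therefore about 2 to 3 percentage points at 5% missed and about 6 to 7 at 10%, under either distribution.

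**Step 2. How many stays change the result if the data match the planned effect?** With usual care at 1.56: 40 × 1.56 = 62 stays, against 62.4/1.79 = 35. Then z = ln(62/35)/√(1/62 + 1/35) = 2.70, p = 0.007. Adding 7 stays to IG (62 versus 42) gives p = 0.051. Removing 9 from usual care (53 versus 35) gives p = 0.057. So 7 to 9 stays are needed.
- If 1.56 is instead the intervention rate (2.79 versus 1.56), 23 added stays are needed at 40 per arm.
- From equal counts of 62, 21 IG stays must disappear (62 versus 41, p = 0.040).

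**Step 3. A near-threshold illustration.** Allowing for the average 25-day inpatient stay (Context and targeted sites), usual care has 40 × 1.56 × 340/365 = 58.1 stays. For 58 versus 40, z = ln(58/40)/√(1/58 + 1/40) = 1.81, p = 0.071. Moving two stays per arm in the favourable direction (60 versus 38) gives z = 2.20, p = 0.028. With dispersion 0.25 in the variance, 60 versus 38 gives z = 0.457/√(1/60 + 1/38 + 0.0125) = 1.94, p = 0.0525, and no longer crosses 0.05.

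**The case against.** **The sentence may mean only patients and carers.** It follows the description of what each arm receives, and group there means IG or usual care. That reading is plausible, and on it the statement is fair. What stands is that the wording is not limited to them.

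**An article may leave adjudication and coded-arm analysis to the full protocol or analysis plan.** True, and their absence alone would be no finding. The point rests on a positive statement of infeasibility that, taken literally, closes off both.

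**The outcome is fairly objective and other safeguards exist.** Allocation is concealed, Table 3 names the EHR as source, the same method is specified for both collectors, and intention-to-treat analysis is planned. This stands. A reader might infer that masking is the only protection left for the primary outcome; the article does not support that.

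**The result is not generally fragile.** A reader might take 58 versus 40 to show that a few reclassified stays decide the trial. That example has a ratio of 1.45, not 1.79, starts just above 0.05, moves all four stays the same way, and fails once dispersion is allowed for. At the planned effect 7 to 9 stays are needed, and more under other readings.

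**Loose definitions and open model choices need pre-specification, not blinding.** Largely right. Masking adds to a written rule and does not replace it.

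**Masking would be partial.** Records may mention APN visits, FIMA comes from unblinded patients, a per-protocol dataset may reveal the arm, and decisions to admit remain unblinded. All of this stands.

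**Conclusion.** The point holds as a cheap improvement, not as a flaw that invalidates the trial. The blinding statement is broader than anything in the article supports: classification of an EHR count and analysis on coded arms can both be masked. The reason to act is that data collection differs by arm, with the intervention's own profession collecting in the IG.

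The size is modest and conditional. If 5% to 10% of IG stays were missed and there were no true effect, the chance of a significant result favouring the intervention would rise from about 4.8% to between 7.5% and 11.4%. This assumes 40 per arm, one year, 1.56 stays per patient-year, negative binomial counts with shape 4, and the Wald test.

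A reader might infer that biased counting is expected, or that the care coordinators themselves decide which stays count. The article says neither. It names APNs as IG collectors and does not say who extracts the admissions from the EHR.

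**What to change.** 1. In Randomization process, limit the sentence to patients and care staff, and state that event classification and the primary analysis are masked.
2. Classify re-hospitalisations in both arms from one hospital admission/discharge listing that carries neither the arm nor SMILe entries. Use one written definition that says which stays count, and align Tables 2 and 3 on the source.
3. Run the primary analysis on coded arms, with the key kept in secuTrial, until the event list, imputation approach and primary model are locked.

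**Cost.** One extra data-handling step: a masked export, made by someone who does not classify the stays, and a coded arm variable. Sample size, patient burden and clinical care do not change.

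**Limits.** Masking will be imperfect where records mention APN visits or a per-protocol dataset reveals the arm. It does not remove bias from unblinded admission decisions or from FIMA self-report, and the trial report should say so.
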